## Abstract

**Background:**

An important parameter for survival in patients with esophageal carcinoma is lymph node status. The distribution of lymph node metastases depends on tumor characteristics such as tumor location, histology, invasion depth, and on neoadjuvant treatment. The exact distribution is unknown. Neoadjuvant treatment and surgical strategy depends on the distribution pattern of nodal metastases but consensus on the extent of lymphadenectomy has not been reached. The aim of this study is to determine the distribution of lymph node metastases in patients with resectable esophageal or gastro-esophageal junction carcinoma in whom a transthoracic esophagectomy with a 2- or 3-field lymphadenectomy is performed. This can be the foundation for a uniform worldwide staging system and establishment of the optimal surgical strategy for esophageal cancer patients.

**Methods:**

The TIGER study is an international observational cohort study with 50 participating centers. Patients with a resectable esophageal or gastro-esophageal junction carcinoma in whom a transthoracic esophagectomy with a 2- or 3-field lymphadenectomy is performed in participating centers will be included. All lymph node stations will be excised and separately individually analyzed by pathological examination. The aim is to include 5000 patients. The primary endpoint is the distribution of lymph node metastases in esophageal and esophago-gastric junction carcinoma specimens following transthoracic esophagectomy with at least 2-field lymphadenectomy in relation to tumor histology, tumor location, invasion depth, number of lymph nodes and lymph node metastases, pre-operative diagnostics, neo-adjuvant therapy and (disease free) survival.

**Discussion:**

The TIGER study will provide a roadmap of the location of lymph node metastases in relation to tumor histology, tumor location, invasion depth, number of lymph nodes and lymph node metastases, pre-operative diagnostics, neo-adjuvant therapy and survival. Patient-tailored treatment can be developed based on these results, such as the optimal radiation field and extent of lymphadenectomy based on the primary tumor characteristics.

**Trial registration:**

NCT03222895, date of registration: July 19th, 2017.

## Background

Survival rates following an esophageal resection for esophageal carcinoma vary from a median of 25 to 74 months [1, 2]. An important parameter for survival is lymph node status [3–12]. The distribution of lymph node metastases depends on tumor characteristics such as tumor location, histology, invasion depth, and on neoadjuvant treatment [13–20]. However, the precise distribution pattern is unknown.

In the Netherlands, among other countries, curative treatment for patients with esophageal carcinoma consists of neoadjuvant chemoradiation followed by surgery [21, 22]. The radiation field during neoadjuvant treatment and the lymphadenectomy during surgery depend on the location of lymph node metastases but no consensus has been reached on the extent of the lymphadenectomy [23]. If a distribution pattern of lymph node metastases of esophageal carcinoma can be identified, the optimal neoadjuvant and surgical treatment can be determined.

The administration of neoadjuvant therapy itself can also influence the distribution of lymph node metastases [13]. Neoadjuvant chemoradiation may be able to sterilize metastatic lymph nodes. Lymph nodes inside the radiation field are affected by both radiotherapy and concurrent chemotherapy, whereas lymph nodes outside the radiation field are affected by chemotherapy only. Nevertheless, recent studies show that also after neoadjuvant therapy, the extend of lymphadenectomy is directly related to survival [24]. Therefore, not only the metastatic behavior of untreated esophageal carcinoma is an important factor, also the pattern after neoadjuvant therapy can provide valuable information for the optimal extend of lymphadenectomy after chemo (radio)therapy.

Especially for adenocarcinoma the distribution of lymph node metastases has not yet been described in large series that report on a complete 2- or 3-field lymphadenectomy [13, 14]. Also, different classification systems for lymph node stations are used in current literature, leading to incomparable studies. Besides the limited and heterogeneous evidence, also the significant morbidity involved in esophageal surgery makes the treatment choices demanding considering that the removal of more lymph nodes may lead to a more invasive procedure, possibly increasing the risk for postoperative morbidity.

A large observational study could identify lymph node stations that should be resected in relation to tumor characteristics and may clarify if the same surgical strategy is justified in patients with and without neoadjuvant therapy. Furthermore, the prognostic value of different lymph node stations can be established. We thus propose a multicenter prospective study to determine the distribution of lymph node metastases in patients with resectable esophageal or gastro-esophageal junction carcinoma in whom a transthoracic esophagectomy with a 2- or 3-field lymphadenectomy is performed. This can be the foundation for a uniform worldwide staging system and establishment of the optimal surgical strategy for esophageal cancer patients.

## Methods

### Objective

The aim of the TIGER study is to evaluate the distribution of lymph node metastases in esophageal carcinoma specimens following transthoracic esophagectomy with a 2- or 3- field lymphadenectomy.

### Study design and setting

TIGER is an international observational cohort study. The duration of the study will approximately be 7 years (2 years inclusion, 5 years follow-up). There are currently 50 participating centers distributed over 18 countries. Centers are located in The Netherlands (10), Sweden (1), Finland (1), Belgium (2), Germany (3), Swiss (1), France (1), Italy (5), Spain (2), United Kingdom (7), Ireland (2), Japan (4), Hong Kong (1), China (1), India (2), United States (5), Canada (1) and Brazil (1). Data from each participating hospital will be collected at the TIGER website (www.tigerstudy.net). Data collection forms can be assessed after login on the website. Each hospital has access to their own dataset.

### Study population

All patients with a resectable (cT1-4a, N0–3, M0) esophageal or gastro-esophageal junction carcinoma.

#### Inclusion criteria

In order to be eligible to participate in this study, a subject must meet all of the following criteria:Primary squamous cell or adenocarcinoma of the esophagus or esophago-gastric junctionSurgically resectable tumor (cT1-4a, N0–3, M0)Adequate physical condition to undergo transthoracic surgery (ASA 1–3)Transthoracic esophagectomy, either open or minimal invasive

#### Exclusion criteria

A potential subject who meets any of the following criteria will be excluded from participation in this study:Previous thoracic or abdominal (upper GI) surgery disturbing lymph drainage of the esophagus and stomachPatients with in situ carcinoma or high-grade dysplasia

### Sample size

The aim is to include 5000 patients. This number suffices for descriptive purposes and clustering of metastases diffusion profiles into meaningful subgroups within predefined strata (patients with adenocarcinoma or squamous cell carcinoma, with and without neoadjuvant therapy, different tumor heights and invasion depths, and following a 2- or 3-field lymphadenectomy). In 2012, the incidence of esophageal cancer was 456.000 new cases worldwide [25]. Only a small percentage of patients with esophageal cancer present with curable disease at time of diagnosis. The aim is to include all 5000 patients with resectable disease in the 50 participating centers in a 2-year time period.

### Primary endpoint

The distribution of lymph node metastases in esophageal and esophago-gastric junction carcinoma specimens following transthoracic esophagectomy with at least 2-field lymphadenectomy in relation to tumor histology, tumor location, invasion depth and neoadjuvant therapy.

### Secondary endpoints

Accuracy of preoperative diagnostics (EUS and PET-CT) and added value of EBUS to existing staging with EUS/PET-CTPrognostic value of different lymph node stationsPostoperative morbidity (anastomotic leakage, chyle leakage, pneumonia, recurrent nerve injury and arrhythmia)30-days/in-hospital and 90-days mortality3- and 5-year overall and disease-free survivalDistribution pattern of recurrence or metastasesIn-field- or out-field nodal recurrence in case of neo-adjuvant chemoradiationNumber of harvested lymph nodes in patients who are treated with and without neo-adjuvant chemo (radio)therapyAnalysis of the phenomenon skip nodal metastasesRatio of nodal metastases inside and outside the radiation field

### Treatment of subjects

#### Staging

Preoperative staging will be performed according to national guidelines. This therefore, may differ per country. Usually, patients are staged with an endoscopy with biopsies, an endoscopic ultrasound, a PET-CT-scan of neck, thorax and abdomen and an ultrasound of the neck. An EBUS-TBNA will be performed if indicated. All patients are discussed in a multidisciplinary team (MDT).

A suspected lymph node is defined as a node larger than > 9 mm short axis or a node 5–9 mm short axis that is round, inhomogeneous and has an irregular border (2 out of 3). In case of PET-CT-scan, pathological nodes are those with FDG uptake, a short axis > 10 mm or those with a short axis between 5 and 9 mm that present with sharp borders.

#### Neoadjuvant therapy

In case of potentially curative disease (cT1-4a, N0–3, M0) patients may be treated with neoadjuvant therapy, this however, may differ per country and usually consists of chemotherapy or chemoradiotherapy.

#### Radiation fields

One coronal, 1 sagittal and 3 axial CT-images of the radiation field is documented in the medical file, to assess lymph nodes stations incorporated in the radiation field. An anatomical description of the radiation field will be given according to highest and lowest radiated lymph node station. An in-field lymph node is defined as a lymph node within the clinical target volume. Clinical target volume fields as defined gross tumor volume plus a margin for sub-clinical disease spread.

#### Restaging

After completion of neoadjuvant therapy patients will generally be restaged with a (PET-)CT scan to exclude distant metastases before patients are scheduled for surgery. In addition, the locoregional lymph nodes will be evaluated. The (PET-)CT will usually be performed 2–4 weeks after completion of neoadjuvant therapy.

#### Surgery

If no metastases are detected, patients will be operated 5–12 weeks after completion of neoadjuvant therapy. This may differ per country and may depend on the type of neoadjuvant therapy. If no neoadjuvant therapy is administered patients are directly scheduled for surgery.

An esophageal resection with a 2- or 3-field lymphadenectomy can be performed via a thoracolaparoscopy, a thoracolaparotomy or a hybrid procedure and a cervical incision as indicated. A gastric tube or colonic interposition can be used for reconstruction. Lymph node stations may be dissected ex vivo (after enbloc resection with the specimen), in vivo, or partially ex and in vivo, and will be separately sent for pathological examination. Lymph node stations in close proximity to the tumor are preferably marked with sutures or beads to prevent damage to the specimen and circumferential resection margin.

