## Discussion

The TIGER study is an international observational cohort study, with participation of worldwide renowned esophageal cancer centers, that will investigate the distribution of lymph node metastases is esophageal cancer. This global study group will be a unique international collaboration that will determine the pattern of lymph node metastases in both squamous cell and adenocarcinoma, since, especially in adenocarcinoma, this has not been investigated in multicenter prospective series before [11, 12]. The results of the TIGER study will provide a roadmap of the location of lymph node metastases in relation to tumor histology, tumor location, tumor invasion depth, number of lymph nodes and lymph node metastases, pre-operative diagnostics, neoadjuvant therapy and survival. In addition, it will be investigated whether neoadjuvant chemoradiotherapy and chemotherapy influence the presence and location of lymph node metastases, as some recent reports suggest that lymph nodes can become sterile after neoadjuvant treatment and only fibrosis is found in these lymph nodes [22]. The prognostic value of positive lymph nodes, micrometastases, isolated tumor cells and fibrosis will be investigated. Patient-tailored treatment can be developed on the basis of the TIGER study results, such as the optimal radiation field and the extent of the lymphadenectomy and, additionally, it may aid in the development of a global uniform classification system.

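### The with/without neoadjuvant contrast among operated patients cannot by itself show whether neoadjuvant therapy influences the presence and location of nodal metastases

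*Protocol article*

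**What the plan says.** Entry depends on the operation. The Methods paragraph of the abstract admits patients "in whom a transthoracic esophagectomy with a 2- or 3-field lymphadenectomy is performed in participating centers will be included", and the Inclusion criteria, all of which must be met, list "Transthoracic esophagectomy, either open or minimal invasive".

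The two treatment paths to that operation differ. Under Restaging: "After completion of neoadjuvant therapy patients will generally be restaged with a (PET-)CT scan to exclude distant metastases before patients are scheduled for surgery". Under Surgery: "If no metastases are detected, patients will be operated 5–12 weeks after completion of neoadjuvant therapy", whereas "If no neoadjuvant therapy is administered patients are directly scheduled for surgery". Who receives neoadjuvant therapy follows local practice: "patients may be treated with neoadjuvant therapy, this however, may differ per country".

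The primary part of the Statistical analysis reports counts and percentages per lymph node station, in separate strata by histology and by neoadjuvant use. The Discussion then sets a further question: "it will be investigated whether neoadjuvant chemoradiotherapy and chemotherapy influence the presence and location of lymph node metastases". The Background adds that a large observational study "may clarify if the same surgical strategy is justified in patients with and without neoadjuvant therapy".

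**The concern.** Whether a therapy influences nodal disease is a causal question, and the contrast on offer has two weaknesses for answering it.

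- **Selection after treatment.** A patient who starts neoadjuvant therapy is seen in this study only if he or she completes it, shows no metastases at restaging and is then operated. No corresponding step stands between a surgery-first patient and the operation. If patients lost on the neoadjuvant path differ in nodal status from those who remain, the two resected groups differ even when therapy does nothing to the nodes.
- **Confounding.** Therapy is chosen by country practice and, presumably, by stage, so the groups can differ before any treatment is given.

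Analysing the groups separately removes neither problem, and no later adjustment recovers patients who never entered. The Discussion expects the results to inform radiation fields and the extent of lymphadenectomy, so a difference produced by selection could be read as sterilization of nodes.

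**Working it through.** **The plan's own figures.** The protocol article gives no node-positivity rate, no proportion not operated after neoadjuvant therapy and no effect size, so there is no stated figure to reproduce on this point. The target of 5000 has no power or precision basis in the text. It equals 50 centers × 2 years × 50 patients per center per year, which is arithmetic only.

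**Illustration under no treatment effect.** All inputs are assumptions:
- p: node positivity among everyone who starts either path, 45% or 50%.
- d: share of neoadjuvant starters not operated, 5% to 20%.
- q: node positivity among those not operated, 50% to 80%.

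Positivity seen in operated neoadjuvant patients is (p − d·q)/(1 − d). The shift from p is therefore d·(p − q)/(1 − d).

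Worked examples:
- p = 0.50, d = 0.10, q = 0.80: (0.50 − 0.08)/0.90 = 46.7%, a shift of −3.3 points.
- p = 0.45, d = 0.20, q = 0.80: (0.45 − 0.16)/0.80 = 36.25%, a shift of −8.75 points.

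Shift in percentage points:

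| p | q | d = 5% | d = 10% | d = 15% | d = 20% |
|---|---|---|---|---|---|
| 50% | 50% | 0 | 0 | 0 | 0 |
| 50% | 65% | −0.8 | −1.7 | −2.6 | −3.8 |
| 50% | 80% | −1.6 | −3.3 | −5.3 | −7.5 |
| 45% | 80% | −1.8 | −3.9 | −6.2 | −8.8 |

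The sign of the shift is the sign of p − q. If those not operated are less often node-positive than average, for example because good responders skip surgery, the shift is positive and the neoadjuvant group looks worse than it is.

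**Against the precision of the study.** With all 5000 patients in one comparison, the 95% confidence interval for the difference has a half-width of 2.8 points (50:50 split) or 3.0 points (70:30, with 70% neoadjuvant). If the groups were tested at the plan's general level of p < 0.05, taken as two-sided, the chance of a significant difference with no treatment effect, at p = 50% and q = 80%, is:

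| Split | d = 5% | d = 10% | d = 15% | d = 20% |
|---|---|---|---|---|
| 50:50 | 20% | 66% | 96% | >99% |
| 70:30 | 18% | 58% | 93% | >99% |

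At q = 65% and a 50:50 split the first three chances fall to 8%, 22% and 47%, and the fourth to 76%. At q = 50% the chance is the nominal 5%. These figures pool both histologies. The plan separates them, so each comparison would be smaller and less likely to reach significance, but the shift itself would not shrink.

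**The case against.** The strongest reply is that the study is descriptive and already limited to resected patients. The Objective and the Primary endpoint concern specimens after transthoracic esophagectomy, the Sample size section speaks of descriptive purposes, and no model or test of a neoadjuvant effect on nodal metastases is stated. The Discussion poses a question and announces no result. This stands, and it confines the point to how that one question is answered and worded.

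Other parts of the reply also stand:
- A reader might infer that the Background's question about surgical strategy is biased too. That question concerns patients who reach surgery, so conditioning on the operation gives the right population.
- A reader might infer that the bias must flatter neoadjuvant therapy. Restaging is only generally done and is meant to exclude distant metastases. Locoregional nodes are evaluated as well, but no nodal rule for withholding surgery is given. A link with nodal status is plausible but not quantified.
- A reader might extend the point to survival. No survival comparison between patients with and without neoadjuvant therapy is stated.
- A reader might call the lack of a count of non-operated patients an omission. The article condenses a fuller protocol, where such a log may sit.
- Some evidence on sterilization does not need the surgery-first group: fibrotic nodes without vital tumor cells are recorded separately (Pathology), and the ratio of nodal metastases inside and outside the radiation field is a secondary endpoint.

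What the reply does not remove is the mismatch between a question about influence and a contrast of two differently selected groups. The fibrosis and radiation-field data also come from operated patients only.

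**Conclusion.** The concern holds in limited form. The contrast between resected patients with and without neoadjuvant therapy is subject to selection after treatment and to confounding by country and indication. By itself it cannot answer whether the therapy influences the presence and location of nodal metastases.

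The size is an assumption throughout. It runs from 0 to about −9 points of node positivity over the ranges shown, with the opposite sign possible. At the larger values the shift exceeds the half-width of the confidence interval, so a big cohort would make it look like a firm finding. The calculation concerns overall positivity and says nothing about how individual stations would be affected.

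The documents do not support concluding that the primary analysis is invalid. The per-station description, stratum by stratum, stands for the population of operated patients.

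**What to change.** 1. In the Statistical analysis (primary parameters) and the Discussion, state that differences between patients with and without neoadjuvant therapy are associations among resected patients and not estimates of a treatment effect.
2. Present the contrast within pre-treatment cT and cN categories and by country or region, in addition to invasion depth. The clinical stage is already needed for eligibility. This reduces baseline differences but does not remove selection after treatment, and the text should say so.
3. Base statements on nodal sterilization on the fibrotic-node records and the in-field versus out-of-field ratio, noting that these too apply to operated patients only.
4. Where centers already hold the figure, report how many patients started neoadjuvant therapy but were not operated, by reason, as context. A formal bounding analysis is not essential. With p = 45% and q = 80%, counting all non-operated patients as negative or as positive gives 37–47% at d = 10% (0.411 × 0.90 = 0.37; + 0.10 = 0.47) and 29–49% at d = 20% (0.3625 × 0.80 = 0.29; + 0.20 = 0.49). These ranges are wider than the bias itself and do not inform station location.

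The cost is a few more tables, some with small cells, and a more cautious conclusion. Eligibility and clinical care do not change.

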#### Lymph node classification systems

Different classification systems are used in different countries to classify lymph node stations around the esophagus: the AJCC 8th edition esophageal cancer staging and the JES 11th edition esophageal cancer staging. In Fig. 1 and Table 1 these classifications have been combined for the purpose of this study.

**Fig. 1 Fig1:**
[figure not shown]
Classification of lymph node stations.

**Table 1 Tab1:** Classification of lymph node stations

Cervical lymph node stations (based on the JES 11th edition esophageal cancer staging)	
1. Superficial cervical lymph nodes	
• Lymph nodes located along the external jugular veins and anterior jugular veins beneath the superficial cervical fascia. • Lymph nodes located around the submandibular glands and parotid glands, and anterior to the mylohyoid muscle. • Lymph nodes located in the pretracheal fatty tissue, extending from the hyoid bone superiorly, to the left brachiocephalic vein inferiorly, including the prethyroidal lymph nodes and the prelaryngeal lymph nodes. • Lymph nodes located along the accessory nerve(s), and anterior to the trapezius muscle.	
2. Cervical paraesophageal lymph nodes	
• Lymph nodes located around the cervical esophagus, including lymph nodes located along the recurrent laryngeal nerve and the cervical paratracheal lymph nodes. The lateral boundary is the medial border of the carotid sheath.	
3. Deep cervical lymph nodes	
• Lymph nodes located around the internal jugular vein and the common carotid artery. • Lymph nodes located from the caudal border of the digastric muscle superior to the carotid artery bifurcation. • Lymph nodes located from the carotid artery bifurcation superiorly to the lower border of the cricoid cartilage inferiorly.	
4. Peripharyngeal lymph nodes	
• Lymph nodes located medial to the carotid sheath, extending from the caudal border of the digastric muscle superiorly to the lower border of the cricoid cartilage inferiorly. Postpharyngeal and parapharyngeal lymph nodes are included.	
5. Supraclavicular lymph nodes	
• Lymph nodes located in the supraclavicular fossa, extending from the lower border of the cricoid cartilage superiorly, to the clavicle inferiorly, including the lower internal deep cervical lymph nodes. The medial boundary is the medial border of the carotid sheath.	
Thoracic lymph node stations (based on the JES 11th edition esophageal cancer staging and the AJCC 8th edition esophageal cancer staging)	
6. Upper paratracheal lymph nodes (right / left)	
• Right: Lymph nodes located around the upper thoracic esophagus posterior to the right vagal nerve. Lymph nodes located along the anterior and lateral wall of the thoracic trachea until the level of the right vagal nerve. Lymph nodes located along the right recurrent laryngeal nerve in the mediastinum. The superior boundary is drawn from the cephalic border of the right subclavian artery to the suprasternal notch. • Left: Lymph nodes located around the upper thoracic esophagus. Lymph nodes located along the anterior and lateral wall of the thoracic trachea until the upper margin of the aortic arch. Lymph nodes located along the left recurrent laryngeal nerve in the mediastinum. The superior boundary is drawn from the cephalic border of the left subclavian artery to the suprasternal notch.	
7. Lower paratracheal lymph nodes (right / left)	
• Right: Lymph nodes located in the tracheobronchial angle and located along the anterior and lateral wall of the thoracic trachea. The superior boundary is the vagal nerve, the ventral boundary the superior caval vein. • Left: Lymph nodes located in the tracheobronchial angle and located along the anterior and lateral wall of the thoracic trachea. Lymph nodes located along the azygos vein arch and the right bronchial artery are included. Lymph nodes along the proximal part of the left recurrent laryngeal nerve along the aortic arch are also included. The superior boundary is the inferior wall of the aortic arch, and the lymph nodes are located in the area surrounded by the medial wall of the aortic arch.	
8. Aortopulmonary window lymph nodes	
• Subaortic and para-aortic nodes lateral to the ligamentum arteriosum. Superior boundary is the lower margin of the aortic arch. Ventral boundary is the pulmonary artery, distal boundary the left main bronchus.	
9. Subcarinal lymph nodes	
• Lymph nodes located caudal to the carina of the trachea. The lateral boundaries are the extended line of both lateral margins of the trachea.	
10. Upper mediastinal paraesophageal lymph nodes • Dissection of the lymph nodes located around the upper thoracic esophagus. From the thoracic aperture until the trachea bifurcation.	
11. Middle mediastinal paraesophageal lymph nodes	
• Lymph nodes located around the middle thoracic esophagus. From the trachea bifurcation to the caudal margin of the inferior pulmonary vein.	
12. Lower mediastinal paraesophageal lymph nodes	
• Lymph nodes located around the lower thoracic esophagus. From the caudal margin of the inferior pulmonary vein to the esophagogastric junction	
13. Pulmonary ligament lymph nodes (right / left)	
• Right: Dissection of the lymph nodes within the right inferior pulmonary ligament. • Left: Dissection of the lymph nodes within the left inferior pulmonary ligament.	
Abdominal lymph node stations (based on the JES 11th edition esophageal cancer staging ans the AJCC 8^th^edition esophageal cancer staging)	
14. Paracardial lymph nodes (right / left)	
• Right: Lymph nodes located immediately adjacent to the gastroesophageal junction, including those along the first branch of the ascending limb of the left gastric artery. • Left: Lymph nodes located immediately adjacent to the gastroesophageal junction, including those along the esophagocardiac branch of the left subphrenic artery	
15. Left gastric artery lymph nodes	
• Lymph nodes along the course of the left gastric artery. Superior boundary is the caudal border of the first branch of the ascending limb of the left gastric artery. Proximal boundary is the origin of the left gastric artery.	
16. Celiac trunk lymph nodes	
• Lymph nodes located around the celiac trunk. Dorsal boundary is the aorta; ventral boundary is the origin of the left gastric artery.	
17. Splenic artery and splenic hilum lymph nodes	
• Lymph nodes from the origin of the splenic artery along its course alongside the pancreatic tail, including those adjacent to the splenic artery distal to the pancreatic tail, and those on the roots of the short gastric arteries and those along the left gastroepiploic artery proximal to its 1st gastric branch.	
18. Common hepatic artery lymph nodes	
• Lymph nodes from the origin of the common hepatic artery along its course until the division into the gastroduodenal and proper hepatic artery.	
19. Hepatoduodenal ligament lymph nodes	
• Lymph nodes along the proper hepatic artery and along the portal vein in the caudal half between the confluence of the right and left hepatic ducts and the upper border of the pancreas.	

In case of a 3-field lymphadenectomy stations 1–19 will be resected and in case of a 2-field lymphadenectomy stations 6–19 will be resected as usual. If not all lymph node stations are resected, patients can still be included in the study, however this has to be documented accurately. A video appendix and definitions of the individual lymph node stations are displayed and available for review on the TIGER study website.

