### Statistical analysis

#### Primary study parameter(s)

Numbers and percentages of resected lymph nodes and lymph node metastases will be given per lymph node station (Fig. 1). Tumor location and invasion depth will be categorized. Patients with adenocarcinoma and squamous cell carcinoma and patients with and without neoadjuvant therapy will be analyzed separately.

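### As printed in Table 1, lymph node stations 6, 7 and 10 overlap, do not meet cleanly on the left and list right-sided structures under station 7 Left, so centers can allocate the same node to different stations of the primary endpoint

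*Protocol article*

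**What the plan says.** The Primary endpoint section names "The distribution of lymph node metastases in esophageal and esophago-gastric junction carcinoma specimens following transthoracic esophagectomy". Under Statistical analysis, Primary study parameter(s), the unit of reporting is the station: "Numbers and percentages of resected lymph nodes and lymph node metastases will be given per lymph node station (Fig. 1". The section on lymph node classification systems says that the AJCC and JES schemes were merged for this study, with Fig. 1 and Table 1 as the result.

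The Table 1 entries at issue are these:

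- Station 6, left entry: "Left: Lymph nodes located around the upper thoracic esophagus". It also takes "Lymph nodes located along the left recurrent laryngeal nerve in the mediastinum". Its nodes along the tracheal wall run down to the upper margin of the aortic arch. The right entry likewise includes nodes around the upper thoracic esophagus, limited to those behind the right vagal nerve.
- Station 7, left entry: "Lymph nodes located along the azygos vein arch and the right bronchial artery are included", then "Lymph nodes along the proximal part of the left recurrent laryngeal nerve along the aortic arch are also included", then "The superior boundary is the inferior wall of the aortic arch". The last sentence goes on to place the nodes in the area enclosed by the medial wall of the arch.
- Station 10: "Dissection of the lymph nodes located around the upper thoracic esophagus", from the thoracic aperture down to the tracheal bifurcation.

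**The concern.** The station label is the outcome variable of this study. If two stations claim the same tissue, or two neighbors do not meet, the label depends on how a center reads the table. The Surgery section has stations dissected in vivo or ex vivo and sent separately, so the label is fixed before the pathologist sees the node.

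There are 50 centers in 18 countries, and the article says that countries use different classification systems and may differ in neoadjuvant treatment. Coding habit could therefore run along with neoadjuvant therapy, one of the factors by which the primary analysis is separated. Enrolling more patients would not remove such a difference. The Background section itself criticizes earlier work because differing classifications made studies incomparable; loose boundaries would bring that problem into this study. Skip metastases, the prognostic value of stations, and the radiation field described by its highest and lowest station rest on the same labels.

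**Working it through.** The article states no figure that could be recomputed here. The check compares the boundaries in Table 1, pair by pair.

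1. **Station 6 against station 10.** Both 6-right (behind the right vagal nerve) and 6-left (no further limit in that sentence) take nodes around the upper thoracic esophagus. Station 10 takes nodes described in the same terms, from thoracic aperture to bifurcation. No sentence excludes one from the other. Result: overlap on both sides.
2. **6-left against 7-left, recurrent nerve.** 6-left takes the nodes along the left nerve in the mediastinum with no lower limit in that sentence. 7-left takes those on the proximal part of the same nerve along the arch. Result: overlap.
3. **6-left against 7-left, trachea.** 6-left ends at the upper margin of the arch; 7-left begins at its inferior wall. Result: the two limits do not meet. 7-left also departs from its own upper limit by including nerve nodes along the arch.
4. **6-right against 7-right.** Both use the vagal nerve as the common limit. Result: no gap. The mismatch is on the left only.
5. **Side.** The azygos arch and the right bronchial artery stand under station 7 Left, and the Right entry does not mention them. Result: a right-named structure under a left heading.

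Thoracic stations run from 6 to 13, which is eight; three of them (6, 7, 10) are affected.

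**Illustration only; both inputs are assumptions.** Suppose 5% of patients in a group have a positive node in the tissue shared by stations 6 and 10, and no other positive node in either. If a share f of these patients is coded to station 6 and the rest to station 10, station 10 reads 5% × (1 − f) and station 6 reads 5% × f. As f runs from 0 to 1, each station ranges over 0% to 5%. For comparison, take n = 5000 / 4 = 1250, which assumes four equal groups by histology and neoadjuvant therapy. The sampling half-width at 5% is 1.96 × √(0.05 × 0.95 / 1250) = 0.012, or 1.2 points. The ends of the range require every center to code the same way, and further strata would widen the sampling interval. The example shows what the wording permits and is not an estimate.

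**The case against.** The strongest reply is that the operative definitions may be elsewhere. The primary analysis refers to Fig. 1, which is missing from the text at hand, and the article points to a video appendix and station definitions on the study website. These may draw the boundaries clearly. That limits what can be said about actual coding. It does not clear Table 1: if those sources are clear, the printed table conflicts with them.

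Other replies stand in part:

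- The recurrent-nerve overlap can be resolved by letting the specific entry (7-left, along the arch) override the general one (6-left). This is reasonable, but the table does not say so.
- A reader might infer that all nodes at arch level have no station. The text does not support this. The nerve nodes there are claimed twice, and the medial-wall clause of 7-left suggests that some tissue beside the arch is meant to belong to it. The doubt is confined to left paratracheal nodes at arch level that do not lie on the nerve.
- A reader might infer that nodes will be counted twice. Stations are sent separately, so a node normally arrives under one label. The risk is different allocation between centers.
- A reader might infer that the laterality of the primary result is wrong. The analysis section says per station and does not mention a split by side; right and left appear only in Table 1. If station 7 is reported whole, the side anomaly leaves its total unchanged.

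**Conclusion.** The point holds for the printed wording. Table 1 contains two overlaps (6 with 10, and 6-left with 7-left), one pair of left-sided limits that do not meet, one entry at odds with its own upper boundary, and one side anomaly. Because the primary result is tabulated by these stations, the boundaries can lead centers to allocate the same node differently. This is a stated rule that contradicts itself, not detail that an article would leave to a longer document.

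The stronger statement, that the primary endpoint is misclassified, is not supported. The article gives no metastasis rates per station and no agreement between centers, so neither the occurrence nor the size of misallocation can be computed. The conclusion rests on Table 1 as printed and assumes that centers may work from it; Fig. 1, the website definitions and the data collection forms were not available.

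**What to change.** In Table 1:

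- Assign nodes around the upper thoracic esophagus to only one of stations 6 and 10.
- Set one common boundary between 6-left and 7-left, and let it also settle the recurrent-nerve nodes.
- Check the azygos and right-bronchial-artery sentence against the source classifications and correct its side. The article alone does not show whether the sentence is misplaced or a side word is wrong.
- Align Table 1, Fig. 1, the website definitions and the data collection forms.

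For data already collected, add a sensitivity table that pools stations 6, 7 and 10 into one upper-mediastinal area and reports station 7 without laterality. Keep the per-station results as primary, because pooling loses the distinction between paratracheal and paraesophageal nodes that the study wants to describe.

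The cost is a corrected table, a note to centers and one extra table. All three stations lie within the 2-field set (6 to 19), so the extent of resection is unchanged.
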